### Data collection and statistical analysis

Therapists will collect the data using Case Report Forms. Two independent researchers will then input the data into the database. All analyses will be carried out under the guidance of independent data monitors to ensure the security and dependability of the data. About the dropped-out participants, their number and the reason for termination will be recorded, especially for adverse events. All enrolled patients will be included in the primary analysis conducted in accordance with the intention-to-treat (ITT) principle. The data will be analyzed by SPSS for Windows version 19.0. The statistical significance is defined as a two-sided *P* value of ≤ 0.05. The baseline characteristics will be reported as the means ± standard deviation (SD). For comparison of baseline materials, a chi-squared or Fisher’s exact test will be used for categorical variables, Student’s *t* test will be used for normally distributed data, and the Mann-Whitney *U* test will be used for non-normally distributed data. The scores of each rating scale and laboratory index before the intervention will be compared between the groups via Student’s *t* test or the Mann-Whitney *U* test. For the comparison within groups, the changes in the scores and indexes from baseline to endpoint will be assessed by a paired *t* test or the Wilcoxon rank-sum test. For the difference between groups, we will use Student’s *t* test or the Mann-Whitney *U* test. For the safety analysis, the adverse events will be listed and analyzed using a chi-squared or Fisher’s exact test. For participants who discontinue or deviate from intervention, listwise deletion or multiple imputation will be used.

The data of fMRI will be analyzed by professional technicians at the Shenzhen Advanced Institute.

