## Abstract

**Background:**

Upper limb and hand motor dysfunction is one of the challenges in rehabilitation after cerebral ischemic stroke (CIS), and the clinical efficacy of rehabilitation needs to be improved. This study aims to combine Jin’s three-needle acupuncture (JTN) therapy with mirror therapy (MT) for hemiplegia after CIS, objectively evaluate the clinical effects and safety of JTN to treat upper limb dysfunction, and use functional magnetic resonance imaging (fMRI) of the brain to investigate the central mechanisms of the effects, which would provide a powerful evidence-based medical basis for further supporting the application of JTN combined with MT.

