**Discussion:**

This study may help to identify the efficacy and safety of acupuncture combined with MT for upper limb dysfunction after CIS and explore the central mechanisms with brain fMRI.

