#### JTN group

In the control group, the acupuncture therapy will be the same as the treatment group’s.

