#### Concomitant treatments

The patients in two groups will be treated with basic medications in the meantime. The patients in two groups will be treated with basic medications according to guidelines for clinical management of cerebrovascular disorders [25] to control blood pressure: individual treatment is adopted to stabilize blood pressure below 135/85 mmHg or within the normal range, control blood sugar and lipid, and prevent platelet aggregation.

The patients in the two groups will be provided with instructions to discourage them from receiving any additional specific complementary treatments related to upper limb dysfunction after CI throughout the trial, including abdominal acupuncture, fire acupuncture, floating acupuncture, and other acupuncture therapies, moxibustion, herbal medicine, massage, etc. If a patient needs other prescription medication, the relevant information will be recorded in the Case Report Form for that patient. The data will be assessed by two blinded researchers, to ensure whether be included.

For follow-up, all participants will participate in a 12-week follow-up after 4 weeks intervention. At the end of a 12-week follow-up period, participants will be referred for clinical evaluation to assess their functional status, including Fugl–Meyer Assessment for Upper Extremity (FMA-UE), motor assessment scale (MAS), action research arm test (ARAT), and activities of daily living (ADL) scale.

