### Outcome measures

The study period is 16 weeks. FMA-UE, MAS, ARAT, ADL, and fMRI will be assessed before and after the treatment, as well as safety indicators such as blood routine test, urine routine test, stool routine test, liver and kidney function examination, and blood glucose. All the patients will take FMA-UE, MAS, ARAT, and ADL assesses after 12 weeks follow-up. Health economic indicators were recorded at week 4 and week 16. All outcomes will be measured by several experienced assessors who are blinded to the randomization group after the baseline visit for evaluation. All assessors will be trained to administer these assessments.

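### Safety laboratory values are tested only for mean or rank change, which is insensitive to one to three patients per arm becoming abnormal; a shift table should be the main summary

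*Protocol article*

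**What the plan says.** Under Outcome measures, the protocol article lists "safety indicators such as blood routine test, urine routine test, stool routine test, liver and kidney function examination, and blood glucose", assessed before and after the treatment.

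Under Data collection and statistical analysis, these values are handled together with the efficacy scales:

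- Baseline: "The scores of each rating scale and laboratory index before the intervention will be compared between the groups via" a t test or Mann-Whitney U test.
- Within arms, where the options named are a t test and a Wilcoxon rank-sum test: "For the comparison within groups, the changes in the scores and indexes from baseline to endpoint will be assessed by a paired". The word indexes refers back to the laboratory index of the sentence before.
- Between arms: "For the difference between groups, we will use Student"'s t test or Mann-Whitney U. This sentence names no variable; on the natural reading it covers both scores and laboratory indexes.

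The only analysis labelled as safety in that section concerns adverse events, which are listed and compared by a chi-squared or Fisher's exact test. The article mentions no reference range and no count of abnormal laboratory values.

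Safety is a stated aim. The Abstract sets out to "objectively evaluate the clinical effects and safety of JTN to treat upper limb dysfunction" and expects the study to help "identify the efficacy and safety of acupuncture combined with MT for upper limb dysfunction after CIS". The Conclusion repeats the aim for both JTN and the combination.

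**The concern.** For a safety laboratory value, the useful result is how many patients developed a new abnormality and how severe it was. A test of mean or rank change does not give this. In a t test, a few extreme values raise the standard deviation along with the mean. In a rank test, they can add only a few high ranks, however extreme they are.

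The within-arm tests carry more weight here than usual. In the control arm, "the acupuncture therapy will be the same as the treatment group"'s, so a between-arm comparison informs only on added mirror therapy. That is a feature of an add-on design, not a mistake, and it serves the aim concerning the combination. But it leaves the laboratory part of the JTN safety aim resting on the within-arm tests. Followed as written, the plan could report no significant laboratory change while up to 3 of 30 patients in an arm (10%) had become abnormal.

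**Working it through.** **Inputs.** From the Sample size section: effective rates of 88.9% and 56.1%, type-1 error 0.05, type-2 error 0.2, 26 patients required per arm, 30 enrolled per arm after 15% dropout. From the analysis section: two-sided P ≤ 0.05. The article gives neither the size of laboratory changes nor reference ranges, so these are assumptions below.

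**The plan's own figure.** With the unpooled normal formula, n = (1.960 + 0.842)² × (0.889 × 0.111 + 0.561 × 0.439) / (0.889 − 0.561)² = 7.85 × 0.345 / 0.1076 = 25.2, so 26 per arm. Then 26 × 1.15 = 29.9, so 30. Both stated figures are reproduced. They matter here only because they set the arm size at 26 to 30.

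**Paired t test, limiting case.** Let k of n patients change by the same amount A and the rest by 0.

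- Mean = kA/n.
- SD = A × √[k(n − k) / (n(n − 1))].
- So t = mean / (SD/√n) = √[k(n − 1)/(n − k)]. A cancels: the result is the same however large the rise.

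| k | n = 30: t | P | n = 26: t | P |
|---|---|---|---|---|
| 1 | 1.00 | 0.33 | 1.00 | 0.33 |
| 2 | 1.44 | 0.16 | 1.44 | 0.16 |
| 3 | 1.80 | 0.08 | 1.81 | 0.08 |
| 4 | 2.11 | 0.043 | 2.13 | 0.043 |

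P ≤ 0.05 needs k = 4, which is 13% of 30 or 15% of 26.

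**Wilcoxon signed-rank test, limiting case.** The k patients hold the k largest positive changes; the other signs are random with probability 0.5 (normal approximation, 20,000 simulations per setting).

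| k | n = 30 | n = 26 |
|---|---|---|
| 0 | 4.7% | 4.8% |
| 1 | 5.0% | 5.0% |
| 2 | 6.8% | 7.0% |
| 3 | 11.2% | 12.0% |
| 4 | 17.0% | 18.9% |

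**The test actually named.** The article says rank-sum, which treats the before and after values as independent samples. Because it ignores pairing, it loses sensitivity when a patient's two values are correlated. I simulated normal values with k patients raised by 10 SD (3,000 runs per setting). At an assumed before-after correlation of 0.8, it rejects in under 1% of trials for k = 1 to 3. At 0.5 the figure is about 1 to 3%, and with no correlation about 5 to 9%.

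**A less artificial model.** All changes are normal, and k patients in one arm are shifted by 3, 5 or 10 SD of change (4,000 runs per setting, 26 and 30 per arm). The ranges of rejection are:

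| k | Paired t | Signed-rank | Two-sample t | Mann-Whitney |
|---|---|---|---|---|
| 1 | 1–5% | 4–5% | 2–5% | 5% |
| 2 | 3–9% | 7–8% | 6–9% | 5–6% |
| 3 | 14–19% | 10–12% | 12–19% | 7–9% |

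One outlying patient is picked up no more often than chance. Three are missed in at least about 80% of trials.

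**Would a test on counts do better?** No. Fisher's exact P for 1, 2 and 3 versus 0 of 30 is 1.00, 0.49 and 0.24, and 6 versus 0 is needed for P < 0.05. This favours a descriptive display over another test.

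**What counts with intervals would show** (Clopper-Pearson 95%):

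- No new abnormality: upper limit 6.0% (0 of 60) or 6.8% (0 of 2 × 26 = 52) pooled; 11.6% (0 of 30) or 13.2% (0 of 26) per arm.
- Three pooled cases: 5.0% of 60 (1.0 to 13.9%) or 5.8% of 52 (1.2 to 16.0%).

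**The case against.** **The methods are legitimate for another question.** A paired test of change addresses systematic drift, which is a proper safety question. Missing isolated outliers does not make it wrong for drift. This stands. A reader might infer that the tests are invalid and must be removed; the documents do not support that, and reporting mean changes without P values would be only a preference.

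**Shift tables usually belong in an analysis plan.** The article is condensed, and an unseen plan may add one. Urine and stool tests often give qualitative results (an assumption), for which a t test could hardly be the whole plan. This stands in part: it cannot be inferred that no summary of abnormal values will exist. But the article does fix a method for the laboratory indexes, and the point concerns how well that stated method suits them.

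**Individual safety handling already exists.** Adverse events are listed, assessed by severity and followed until stable. This reduces the importance of the point. It does not remove it, because the article does not say that a laboratory abnormality counts as an adverse event, and its list of possible acupuncture events contains none.

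**Counts cannot settle the JTN safety aim.** Correct. There is no unneedled arm. Time since stroke and the background treatment, which aims to control blood pressure and also to "control blood sugar and lipid, and prevent platelet aggregation", can themselves change laboratory values. A pooled count would describe frequency and not attribute cause.

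**Conclusion.** The point holds as a minor one. The only laboratory analysis that the article names consists of tests of mean or rank change. These suit drift but are insensitive to one to three patients per arm becoming abnormal: limiting-case paired t P = 0.33, 0.16 and 0.08, and signed-rank rejection of about 5%, 7% and 11 to 12%. The paired t figures rest on an idealised pattern (identical rises, all others unchanged). The normal model with shifts of 3 to 10 SD, itself an assumption, leads to the same conclusion. Naming the rank-sum test for within-patient change is a small separate error; signed-rank is the paired version.

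Two stronger readings should be resisted. One is that the between-arm comparison is flawed because both arms receive acupuncture. It answers a question about added mirror therapy, which is what this design can answer. The other is that the trial's safety monitoring fails. Adverse events have their own analysis, and nothing here bears on how they are recorded. No efficacy conclusion or sample size changes.

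**What to change.** Make the main laboratory safety summary a descriptive shift table from baseline to week 4 against the hospital laboratory's reference ranges, by arm and pooled. For each test give:

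- the number of patients normal at baseline and abnormal at week 4;
- the number with a new clinically significant abnormality;
- exact 95% confidence intervals, with patients who have both measurements as the denominator;
- a listing of the clinically significant cases.

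Keep the tests of change as a supporting check for drift, with rank-sum corrected to signed-rank for the within-arm comparison. Add that a nonsignificant result is not evidence of laboratory safety, that the counts describe frequency under acupuncture with and without mirror therapy and do not attribute cause, and that the between-arm comparison concerns added mirror therapy.

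The cost is one paragraph of wording and a few extra tables from tests already taken, with no new visits, procedures or staff. The downside is that isolated abnormalities will need individual comment.

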#### Primary outcomes

The primary outcomes in this study are the mean change in the scores on the FMA-UE from baseline to 4 weeks intervention and 12 weeks follow-up, as well as fMRI between the two groups and within groups from baseline to 4 weeks intervention.

FMA-UE is widely used for motor function assessment and can reflect the functional level of stroke subjects. The upper extremity has a maximum score of 66 points divided into three parts, namely shoulder arm (36 points), wrist hand (24 points), and coordination (6 points) and higher score indicate better upper limb movement function [4]. The FMA-UE is the most common scale for evaluating upper limb motor function after CIS. It is often used as a gold standard for testing the validity of other scales as well [26, 27]. The FMA-UE has excellent reliability and validity and is sensitive enough for clinical and research practice [28].

fMRI is a noninterventional imaging technique that uses magnetic resonance to measure changes in brain hemodynamics caused by neuronal activity as a reflection of the activation state of brain areas. For the observation methods, after the patients are ready, scanning will be performed on the whole brain of the patients. During resting-state scanning, patients will be instructed to relax, close their eyes, and avoid systematic thinking activities as much as possible. After resting-state scanning for 6 min, functional state scanning will be performed. The experimental task will be designed in blocks. There will be 10 trials for each task state (Fig. 3), and the time of each trial is 30 s. In addition, there are 10-s empty sweeps before each scan, so each scan is 5 min and 10 s. Once in place, the subjects will be put on noise-canceling earphones and receive instructions. Patients will be asked to try to imagine their fingers flexing when they hear the word “close.” When they hear the word “open,” they will be asked to try to imagine their fingers straightening. Each subject will receive task training in advance.

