### Sample size

The sample size was calculated based on the effective rate of the treatment. Based on similar previous studies [30], we assumed the effective rate of 88.9% and 56.1% in the JTN+MT group and the control group, respectively. The PASS11.0 software was used to perform a power analysis to determine the sample size. Type-1 error was assumed at 0.05, type-2 error at 0.2. The required sample size was 26 subjects for each group. Considering a dropout rate of 15%, a total of 60 subjects needed to be enrolled (30 participants per group).

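### The non-parametric test named for within-group before/after changes is the rank-sum test, which is for independent samples; the paired counterpart is the signed-rank test

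*Protocol article*

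**What the plan says.** The section Data collection and statistical analysis of the protocol article gives separate rules for within-group and between-group comparisons.

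- Within groups, the sentence begins "For the comparison within groups, the changes in the scores and indexes from baseline to endpoint will be assessed by a paired", which refers to the paired *t* test. It then gives the non-parametric alternative in the words "test or the Wilcoxon rank-sum test".
- Between groups: "For the difference between groups, we will use Student’s" *t* test, with the Mann-Whitney *U* test as the alternative. The same two tests are named for comparing baseline scores and laboratory indices between the arms.
- Significance level: "The statistical significance is defined as a two-sided" *P* value of 0.05 or less.

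The section Outcome measures confirms that the same patients are measured twice: "FMA-UE, MAS, ARAT, ADL, and fMRI will be assessed before and after the treatment". The laboratory safety tests follow the same before-and-after schedule. The data for the within-group comparison are therefore paired.

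**The concern.** The Wilcoxon rank-sum test and the Mann-Whitney *U* test are the same procedure under two names. It compares two independent samples. The article therefore assigns one independent-samples test to two different designs: correctly to the comparison between arms, and incorrectly to the comparison of each patient with himself or herself.

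Applied to paired values, the test treats the baseline scores and the later scores as coming from different people. It sets the shift against the full spread between patients and takes no credit for the part of that spread which cancels within a patient. With positive correlation, the usual case for repeated scores, the p-value is too large.

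At stake are the within-group results for FMA-UE, MAS, ARAT and ADL and, since the sentence covers scores and indexes, apparently the laboratory values too. Modest real changes could often be reported as non-significant.

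**Working it through.** **The plan's own figure, for context.** The section Sample size states: "we assumed the effective rate of 88.9% and 56.1% in the JTN+MT group and the control group, respectively"; and: "Type-1 error was assumed at 0.05, type-2 error at 0.2". The unpooled normal approximation, two-sided, gives n = (1.960 + 0.842)² × (0.889 × 0.111 + 0.561 × 0.439) / (0.889 − 0.561)² = 7.85 × 0.345 / 0.1076 = 25.2, which rounds up to the stated 26 per group. This is a between-group calculation on proportions. It does not involve the within-group test, so the present point does not change it.

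**Inputs for the check.**
- Pairs per group: 30 enrolled, with 26 as the evaluable number (Sample size).
- Two-sided 0.05 (Data collection and statistical analysis).
- Before/after correlation: not given, so it is an assumption, shown from 0 to 0.9.
- Size of the within-group gain: not given, so it is an assumption, shown from 0 to 1.0 SD.
- Distribution: bivariate normal with equal variances, an assumption made for illustration.

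**Type I error by formula.** For paired data with no change, the large-sample variance of the rank-sum statistic is 1 − ρs times the variance that the test assumes, where ρs is the rank correlation. For normal data with correlation ρ, ρs = (6/π) arcsin(ρ/2). The true error is then 2Φ(−1.96/√(1 − ρs)).
- ρ = 0: ρs = 0, error 2Φ(−1.96) = 0.05.
- ρ = 0.5: ρs = 0.483, 1.96/√0.517 = 2.72, error 0.006.
- ρ = 0.7: ρs = 0.683, 1.96/√0.317 = 3.48, error 0.0005.

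**Type I error by simulation (10,000 runs per setting).**

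| Correlation | Rank-sum, n = 30 | Signed-rank, n = 30 | Rank-sum, n = 26 |
|---|---|---|---|
| 0 | 0.049 | 0.051 | 0.050 |
| 0.5 | 0.006 | 0.044 | 0.007 |
| 0.7 | 0.0008 | 0.049 | 0.0012 |
| 0.8 | 0.0001 | 0.050 | 0.0002 |
| 0.9 | 0.0000 | 0.053 | 0.0000 |

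The formula and the simulation agree. The rank-sum test has its nominal size only at zero correlation.

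**Power by simulation, n = 30, rank-sum against signed-rank.**

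| Gain | Correlation 0 | 0.5 | 0.8 |
|---|---|---|---|
| 0.4 SD | 0.32 / 0.31 | 0.25 / 0.55 | 0.19 / 0.90 |
| 0.5 SD | 0.46 / 0.46 | 0.44 / 0.74 | 0.43 / 0.99 |
| 0.8 SD | 0.84 / 0.83 | 0.91 / 0.99 | 0.98 / 1.00 |

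At a gain of 1.0 SD both tests reach at least 0.96 at every correlation tried. The loss is large for small to moderate gains at moderate to high correlation. It is absent at zero correlation and small for large gains.

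**The case against.** **It is probably a slip.** The test stands beside a paired *t* test, in a sentence about change within patients, and the article uses the name Mann-Whitney wherever it means the independent-groups rank test. The paired Wilcoxon test was likely intended. This stands as an explanation, and if the analyst runs the signed-rank test no p-value is harmed. It does not remove the error, because the text names a specific wrong test and no other section corrects it.

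**The illustration is normal, while rank tests are kept for non-normal data.** This stands in part. The article states that condition for baseline comparisons, and it is natural to read it across. The rank-sum result does not change under a common increasing transformation of all values, so its type I error figures also hold for skewed data obtained in that way. The signed-rank power figures do not carry over in the same way, and ties on bounded scales were not simulated. The power figures are therefore illustrative.

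**Stronger readings that a reader might infer.**
- That false claims of benefit follow. They do not: with positive correlation the error is conservative.
- That real changes, including laboratory safety changes, would simply be missed. Small gains often would be; large ones mostly would not. Safety detection does not rest on this p-value either, since adverse events are evaluated by physicians and compared by chi-squared or Fisher's exact test.
- That a primary outcome is affected, because the section Primary outcomes lists "as well as fMRI between the two groups and within groups from baseline to 4 weeks intervention". The sentence at issue covers scores and indexes, and the article hands the fMRI data to separate technicians, so the document does not show that this test would be applied to them.

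**Conclusion.** The text is wrong as written, with limited consequences. Followed literally, an independent-samples test would be applied to paired data. Its p-values would be too large whenever before and after values are positively correlated, and power could fall from 0.55 to 0.25 (correlation 0.5) or from 0.90 to 0.19 (correlation 0.8) for a 0.4 SD gain with 30 pairs. These sizes rest on assumed correlations, gains and normality, none of which the article supplies; at correlation 0 the two tests agree.

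The error reaches only the within-group comparisons of rating scales and laboratory indexes for which the non-parametric option is used. The comparison of the combination with acupuncture alone has suitable tests of its own and is not touched.

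**What to change.** In the section Data collection and statistical analysis, replace Wilcoxon rank-sum test with Wilcoxon signed-rank test in the sentence on within-group comparisons. The Mann-Whitney *U* test stays as it is for comparisons between the arms.

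The cost is one term in one sentence. No additional data are needed, and no sample-size figure or between-group analysis changes. Whether within-group comparisons should also be labelled descriptive is a separate question. It would reach further than this correction, because a within-group fMRI comparison is listed among the primary outcomes, and the correction does not depend on it.

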### Inclusion criteria

The inclusion criteria include the following: (1) corresponding to the diagnostic standards of CIS [18]; (2) corresponding to the diagnostic standards of stroke of TCM [19]; (3) diagnosed with CIS and confirmed by CT or MRI; (4) first-ever clinical CIS occurred ≥ 2 weeks and ≤ 6 months previously, the number of times ≤ 2; (5) aged between 40 and 75, male or female; (6) limb function in NDS [20] score ≥ 10; (7) stable vital sign and consciousness; (8) normal test result of kinesthetic and imagery questionnaire [21]; and (9) provided written informed consent to participate.

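### The between-group test on FMA-UE change is not adjusted for baseline FMA-UE; ANCOVA would be at least as precise, apart from one degree of freedom, at almost no cost

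*Protocol article*

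**What the plan says.** Under Data collection and statistical analysis, the group comparison is fixed by the sentence beginning "For the difference between groups, we will use", which names a Student's t test or the Mann-Whitney U test. No covariate or model is mentioned.

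Under Primary outcomes, the clinical variable is a change score: "The primary outcomes in this study are the mean change in the scores on the FMA-UE from baseline to 4 weeks intervention", and also to the 12-week follow-up. The statistical section does not itself say whether the group comparison is made on change or on follow-up scores. Read with the outcome definition, it is most naturally on change.

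Baseline values will exist. Outcome measures states: "FMA-UE, MAS, ARAT, ADL, and fMRI will be assessed before and after the treatment". Apart from forming the change score, their only stated between-group use is a significance test before treatment: "The scores of each rating scale and laboratory index before the intervention will be compared between the groups". No consequence of that test for the outcome analysis is given.

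**The concern.** The baseline value of a scale is usually among the best available predictors of its later value. A comparison of change fixes the weight given to baseline at exactly 1, whereas ANCOVA estimates that weight from the data. If the true weight is below 1, the change score over-corrects: the arm that happens to start higher is put at a disadvantage, and the estimate has more variance than it needs.

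The trial is small, with 30 patients per group, so chance differences at baseline will not be negligible. Eligibility is also broad in time since stroke ("first-ever clinical CIS occurred ≥ 2 weeks and ≤ 6 months previously"), which makes varied starting levels plausible, although the article gives no figure for this. Testing baseline scores between groups does not alter the treatment estimate, and at this size a non-significant result does not show that the groups are balanced. At stake are the precision of the estimate and its accuracy given the imbalance that actually occurs.

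**Working it through.** **Inputs from the article.** 30 per group, 26 before dropout; 1:1 allocation; "Type-1 error was assumed at 0.05, type-2 error at 0.2"; two-sided testing ("The statistical significance is defined as a two-sided" P value); assumed effective rates of 88.9% and 56.1%.

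**Inputs not in the article.** FMA-UE SDs before (s1) and after (s2) treatment, the correlation rho, and the expected difference in FMA-UE change. I assume rho from 0.5 to 0.9, take s1 = s2 first, and then relax that.

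**1. The plan's own figure.** With unpooled variance, n = (1.960 + 0.842)² x (0.889 x 0.111 + 0.561 x 0.439) / (0.889 - 0.561)² = 7.849 x 0.3450 / 0.1076 = 25.2, so 26 per group, as stated. 26 x 1.15 = 29.9, so 30 per group. This calculation concerns a proportion of responders and says nothing about the power of a test on mean FMA-UE change.

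**2. Relative variance, equal SDs.** Per-patient variance is 2s²(1-rho) for change and s²(1-rho²) for ANCOVA. The ratio of ANCOVA to change is (1+rho)/2. For comparison, the ratio of ANCOVA to a test on follow-up scores alone is 1-rho².

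| rho | ANCOVA / change | ANCOVA / follow-up score |
|---|---|---|
| 0.5 | 0.75 | 0.75 |
| 0.7 | 0.85 | 0.51 |
| 0.8 | 0.90 | 0.36 |
| 0.9 | 0.95 | 0.19 |

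**3. Relative variance, unequal SDs.** The general ratio of ANCOVA to change is s2²(1-rho²) / (s1² + s2² - 2 rho s1 s2). With s2 = 1.25 s1:
- rho 0.5: 1.5625 x 0.75 / (2.5625 - 1.25) = 1.172 / 1.3125 = 0.89
- rho 0.7: 0.797 / 0.8125 = 0.98
- rho 0.8: 0.5625 / 0.5625 = 1.00

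At rho 0.8 the gain disappears, because the ANCOVA slope rho x s2/s1 is then exactly 1, which is the weight the change score uses.

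**4. Power, as an illustration.** Suppose the change-score test had 80% power. ANCOVA power is then Phi(2.802 / sqrt(ratio) - 1.960): 0.90 at rho 0.5, 0.86 at 0.7, 0.84 at 0.8 and 0.82 at 0.9. Simulation with equal SDs at 30 per group (20,000 runs per setting, t-based tests) gave, for change against ANCOVA, 79% against 89%, 84%, 82% and 80% respectively. Type I error was about 5% for the follow-up, change and ANCOVA tests alike.

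**5. Chance imbalance.** The baseline mean difference has SE sqrt(2/30) = 0.26 SD; the chance that it exceeds 0.25 SD in either direction is 33%, and 0.5 SD, 5%. With equal SDs, a baseline difference D moves the estimate by -(1-rho) x D under change scores, by +rho x D under follow-up scores, and by about 0 under ANCOVA. At rho 0.8:
- D = 0.26 SD: change -0.2 x 0.26 = -0.05 SD; follow-up +0.8 x 0.26 = +0.21 SD
- D = 0.5 SD: change -0.10 SD; follow-up +0.40 SD

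**The case against.** The strongest case against is that nothing is broken. A two-sample test on change scores is valid, a rank test is foreseen for non-normal data, and covariate adjustment is often set out in an analysis plan that is not shown here. Validity stands. The last argument does not remove the point, because the article names the test it will use, and the comment is on that stated choice.

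Four stronger readings are tempting, and the document does not support them.

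- *Baseline imbalance is left uncorrected.* The outcome is change from baseline, so baseline is subtracted for every patient. With equal SDs this over-corrects, by (1-rho) x D. Imbalance would be wholly uncorrected only if follow-up scores were compared, which the statistical section leaves open but the outcome definition argues against.
- *The planned test is biased or inflates type I error.* Over all randomisations it is unbiased, and its type I error is about 5% in simulation. The shift by a given D is conditional on the imbalance that occurred.
- *The trial's power would rise from 80% to 90%.* The stated 80% belongs to the effective rate, and no power is stated for mean FMA-UE change. The gain also depends on equal SDs, and step 3 shows that it can vanish.
- *Time since stroke must also be adjusted for.* The article gives no figure for its prognostic strength, and the baseline data listed under Recruitment procedures do not name it. That it is recorded can only be inferred from the eligibility window.

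**Conclusion.** The point holds as a modest and nearly free improvement to a stated method. It is not an error that threatens validity. Relative to a t test on change, ANCOVA reduces variance by 25% to 5% for rho 0.5 to 0.9 if the SDs before and after are equal, and by less, or not at all near rho 0.8, if the follow-up SD is 1.25 times the baseline SD. It also removes, approximately, the residual effect of chance baseline imbalance, which under change scores is small at high rho (0.05 SD for a one-SE imbalance at rho 0.8).

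The true size cannot be fixed from the article, because no SD or correlation is given. The variance figures apply to the t test; no corresponding figure was derived for the Mann-Whitney test. The direction is secure: apart from one degree of freedom, ANCOVA does not lose precision. The stated sample size is unaffected.

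**What to change.** For each between-group comparison of FMA-UE, MAS, ARAT and ADL, at the end of treatment (week 4) and at the end of follow-up (week 16), prespecify ANCOVA of the follow-up score on treatment group with that scale's own baseline value as covariate. Report the adjusted mean difference with its 95% CI. Keep the Student's t or Mann-Whitney test as a sensitivity analysis, and state that it is made on change scores. Do not use the baseline significance tests to judge balance or to decide on adjustment. Time since stroke onset may be added as a covariate if it is recorded.

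The cost is a change of analysis wording. The baseline scores are already scheduled, the named software fits the model, and no patients or visits are added. According to the Blinding section, the allocation code stays closed until the statistical analysis is complete, so the model can be fixed before results by arm are known. Which endpoint and which visit is primary is a separate matter that this change does not settle.
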